## 6.2 Randomisation, blinding and treatment allocation

Randomisation will be performed before the start of the study on the level of preschools within participating childcare organisations. The randomisation will be performed by an independent researcher of the AUAS with the use of computer-generated randomisation lists. It concerns a stratified randomisation by childcare organisation to achieve balance in the number of preschools within each organisation that will receive the intervention or not. As preschools within each organisation differ in location size (and therefore the number of eligible participants), we will 1) order preschools by location size, 2 ) match preschools in pairs based on location size and 3) randomly allocate 1 preschool to the intervention group and the other to the control group. 1 member of the research staff ([name]) will be blinded for allocation and perform final analyses. ECEC teachers, parents and other members of the research staff will not be blinded as the intervention does not allow for this.

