## CHILDREN

At baseline and 6 months, children's height, weight and waist circumference will be measured at preschools. In addition, (some) children will wear an accelerometer for 7 consecutive days. Height (cm) will be measured to the nearest 0.1 cm in standing position using a portable stadiometer (Seca 213). Weight (kg) will be measured to the nearest 0.1 kg in standing position without shoes or heavy clothing using a portable weighing scale (Seca 813). BMI ( $\text{kg/m}^2$ ) will be calculated and BMI z-scores will be assessed using World Health Organisation reference data (WHO Anthro). Waist circumference (cm) will be measured to the nearest 0.1 cm in standing position (at the mid-point between the lower costal margin and the level of the anterior superior iliac) with a standard tape measure (28). All procedures will be performed using Standard Operating Procedures by trained research staff/students of the AUAS. Physical activity will be assessed using a 3-axis accelerometer: ActiGraph GT3X+ (29). The accelerometers will be placed on the right hip using an elastic belt. Children will wear the accelerometers for 7 consecutive days during waking hours, excluding activities including water such as bathing/showering and swimming. Data will be derived using a 10-s epoch. Counts per minute based on vector magnitude will be extracted. In times

of corona, physical measurements at preschools will not be performed as parents and researchers are not allowed to enter the preschools. When it is allowed again to enter preschools, the researchers will start performing the measurements and collect data on children's weight development and physical activity levels.

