#### **9.4 Benefits and risks assessment, group relatedness**

Participants in the control group do not receive the intervention during the study. Benefits for ECEC teachers in the intervention group include the training (professional development) and Toolkit CO-HEALTHY which may improve the collaboration with parents regarding eating, physical (in)activity and sleeping behaviours of children. Both, the training and Toolkit are free of charge. Benefits for parents and children in the intervention group include the parent-child activities regarding eating, physical (in)activity and sleeping behaviours, which may improve the parent-child relationship and may have a positive effect on child development. The parent-child activities and related materials are free of charge.

The risks involving in this study are minimal. ECEC teachers are used to provide parent-child activities at preschools. In this study, specifically activities about eating, physical (in)activity and sleeping behaviours will be supervised. In total, 6 parent-child activities will be carried out by a local team of ECEC teachers during existing contact moments at preschools.

This study can only be performed by including children (minors, aged 2-4 years old), as the intervention is intended to reach children. It is aimed to examine the effects of the intervention on child level (eating behaviours/ physical (in)activity behaviours/sleeping behaviours/anthropometric measures). The risks and burden for children are minimal.

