## 10. ADMINISTRATIVE ASPECTS, MONITORING AND PUBLICATION

### 10.1 Handling and storage of data and documents

Data collection will be carried out by trained research staff and students of the AUAS. New quantitative and qualitative data will be collected at preschools with play-based education in Amsterdam. Data collected on paper questionnaires and score forms (with data of the height/weight/waist circumference measurements) will be entered twice by different staff/students (double data entry) in Microsoft Excel (.xlsx files). In times of corona, a digital version of the ECEC teacher questionnaire will be distributed via Qualtrics. The Qualtrics software is available for all employees of the AUAS and the Dutch AUAS-template in Qualtrics will be used. To protect the privacy of the participating ECEC teachers, an anonymous link to the Qualtrics questionnaire will be mailed to the private work e-mail address of ECEC teachers. In the first question of the digital version of the questionnaire, ECEC teachers will be asked to fill in their own participant number. Short interviews (with ECEC teachers and parents) and 24 hour dietary recalls will be recorded with Olympus Digital Voice Recorders (VN-731PC) and stored as .wma audio files. The short interviews will be held by telephone. The telephone will be set on speaker mode to make it possible to record the short conversations via the Digital Voice Recorders. After the interview, the noted telephone number of a parent will be destroyed. Pseudonymised transcripts will be made in Microsoft Word (.docx format). ActiLife software will be used to handle ActiGraph data (.agd/.csv files). IBM SPSS Statistics will be used for quantitative data analysis. MAXQDA will be used for qualitative data analysis.

All paper and electronic data files will be coded and therefore privacy of the participants will be protected:

- all locations will receive a unique location number (ascending, starting from 001);
- all ECEC teachers will receive a unique code starting with a location number followed by digit '1' (to indicate it concerns an ECEC teacher) and a three-digit participant number (ascending, starting from 001);
- all parents will receive a unique code starting with a location number followed by digit '2' (to indicate it concerns a parent) and a three-digit participant number (ascending, starting from 001). Children will receive the same code as their parents.

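### The reason given in section 6.2 for leaving research staff unblinded does not cover staff or students whose only task is to measure children or run 24-hour recalls

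*Protocol*

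**What the plan says.** Protocol section 6.2 states that one member of the research staff "will be blinded for allocation and perform final analyses". Teachers and parents are unblinded, and "other members of the research staff will not be blinded as the intervention does not allow for this". No other reason is given anywhere in the protocol. The same section says that "Randomisation will be performed before the start of the study on the level of preschools within participating childcare organisations", so the allocation already exists at the baseline visit.

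On who does what:

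- **Delivery.** Section 9.4 has the activities carried out by "a local team of ECEC teachers during existing contact moments at preschools". Section 5.1 likewise has trained teachers pass the content on to their colleagues, who then run the activities.
- **Anthropometry.** Section 6.3 (Children): "All procedures will be performed using Standard Operating Procedures by trained research staff/students of the AUAS". On waist: "Waist circumference (cm) will be measured to the nearest 0.1 cm in standing position", with a tape, at a midpoint between two bony landmarks.
- **Recall and data collection in general.** Section 10.1: "Data collection will be carried out by trained research staff and students of the AUAS", and "24 hour dietary recalls will be recorded with Olympus Digital Voice Recorders".

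**The concern.** The stated reason is a claim about what the intervention permits. For teachers, who run the activities, and parents, who take part in them, it is plainly true. For a person holding a tape measure or asking about yesterday's meals it does not follow, because that person has no part in delivering the programme.

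Some child outcomes depend on the observer. Waist is read to 0.1 cm at a site located by hand on a child of 2 to 4 years. The recall is a conversation in which follow-up questions can differ according to what the interviewer expects. An assessor who knows the arm could, without intending to, shift either one in favour of a healthy-lifestyle programme. Dietary intake and waist circumference are both named secondary objectives (section 2), and section 9.4 cites effects at child level, including anthropometry, as part of the case for including minors.

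**Working it through.** **Does the reason reach the assessors?**

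| Group | Role in the protocol | Does the intervention require knowing the arm? |
|---|---|---|
| Teachers | Receive training, run activities (5.1, 9.4) | Yes |
| Parents | Take part, receive materials (5.1) | Yes |
| Staff holding toolkit interviews | Interview intervention-arm teachers and parents about the toolkit (6.1.2, 6.3) | Yes |
| Staff or students who only measure or run recalls | Anthropometry and recalls (6.3, 10.1) | No |

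The protocol does not describe the last group as a separate team. It also does not say that the tasks must be combined.

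**Do other features prevent concealment?** The randomisation is done by an independent researcher (6.2). Participant codes consist of location number, role digit and participant number, with no arm indicator (10.1). Parent interviews are held by telephone (6.3, 10.1), so they can be kept apart from measurement. At baseline no activity has yet taken place.

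**The plan's own figure.** Section 4.4 gives 160 children per group, cluster size 6, ICC 0.02, 15% drop-out and a detectable d of 0.35 at 80% power.

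- Design effect = 1 + (6 − 1) × 0.02 = 1.10
- Completers = 160 × 0.85 = 136 per arm
- Effective size = 136 / 1.10 = 123.6 per arm
- Detectable d = (1.960 + 0.842) × sqrt(2 / 123.6) = 0.356; power at d = 0.35 is 78.6%

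This agrees closely with the stated figure, and blinding assessors would not change it.

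**Illustration of what a differential shift would do.** The shifts are assumed; the documents give none.

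- SE of a standardised difference = sqrt(2 × 1.10 / 136) = 0.127
- Error rate = P(|Z + shift / SE| > 1.96)

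| Assumed shift (SD) | 136 per arm, SE 0.127 | 60 per arm (assumed opt-in subsample), SE sqrt(2 × 1.10 / 60) = 0.191 |
|---|---|---|
| 0 | 5% | 5% |
| 0.10 | 12.3% | 8.2% |
| 0.15 | 21.8% | 12.3% |
| 0.20 | 34.9% | 18.1% |

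The second column keeps the design effect at 1.10 for simplicity.

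**What the illustration leaves out.** Section 8 adjusts for the baseline value; the table does not. Ignoring clustering, and with a baseline to follow-up correlation r and equal variances, there are two cases:

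- *Shift at 6 months only.* The bias is unchanged and the SE is multiplied by sqrt(1 − r²), so the error rate is higher than tabulated.
- *Same shift at both visits.* The bias is multiplied by (1 − r), so the ratio of bias to SE is multiplied by sqrt((1 − r) / (1 + r)) and the error rate is lower than tabulated.

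Because allocation precedes baseline, either case could arise.

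**The case against.** The best defence is practical. All assessments take place at preschools (6.3), among teachers and parents who know their arm. Depending on the activities chosen, a calendar or the children's placemats may be on the classroom wall (5.1). The same institution recruits, collects questionnaires, interviews teachers and asks intervention-arm parents for an interview. The authors may simply have judged that staff would find out. This part stands: unmasking at 6 months is likely at some sites, and any blinding will be partial. It does not rescue the stated reason, which refers to the intervention rather than the setting, and it has little force at baseline.

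The recall is a weaker example than waist. The parent who reports is unblinded and, in the intervention arm, has been exposed to messages about food. A masked interviewer removes differential probing but leaves the parent's own reporting bias, which may well be the larger problem. Audio recording would also allow probing to be checked. Height and weight, taken with a stadiometer and a scale under standard procedures, are less exposed than waist.

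A reader might infer that assessors could be kept fully unaware at no cost. The documents do not support that: they give no staffing numbers, and separating tasks takes planning. A reader might also take the error rates as an estimate of actual bias. They are not, because the shifts are assumed, full measurement is assumed, and the planned baseline adjustment is not modelled.

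**Conclusion.** The point holds in a limited form. Section 6.2 gives a reason that is valid for teachers and parents and applies it to all research staff except the analyst. It does not cover people whose only task is measuring children or conducting recalls, and the protocol offers no other reason for leaving them unblinded.

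The consequence is an avoidable risk of observer bias, chiefly in waist circumference and in recall probing. Its size cannot be derived from the documents; the tabulated rates only show how sensitive a comparison of this size would be. The affected outcomes are secondary, the recall is optional, and these measurements are suspended in times of corona, so the numbers measured may fall below 136 per arm.

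It would be wrong to read this as a threat to the primary outcome that assessor blinding could cure. Partnership is scored from questionnaires completed by unblinded teachers and parents, and blinding assessors does nothing for it. Nor do the documents show that bias will occur. The finding supports a worthwhile, low-cost improvement and no more.

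**What to change.** Revise section 6.2 to limit the stated reason to teachers, parents and staff who train or interview about the toolkit. Then add that, within the existing pool of staff and students, those who take anthropometry (chiefly waist) or run 24-hour recalls:

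- are not told the allocation at baseline or at 6 months, where feasible;
- do not give the training or hold toolkit interviews;
- measure before any toolkit interview takes place at that site;
- record, for each visit, whether they became aware of the arm.

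If this is judged impossible, section 6.2 should give a reason specific to assessors. It should also acknowledge that parental reporting bias in the recall remains.

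The cost is some task planning. The downside is that blinding will be partial, because displayed material or conversation with teachers and parents may reveal the arm. For any site where measurements are still waiting for access to return, the change can be made before they begin.

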### 6.3 Study procedures

The study period will be 6 months, starting with a baseline measurement and ending with a close-out measurement. All assessments will take place at preschools in Amsterdam, the Netherlands. In times of corona, only questionnaires will be distributed as other measurements at preschools are not allowed.

#### ECEC TEACHERS

At baseline and at 6 months, participating ECEC teachers will be provided with a paper questionnaire. In times of corona, a digital version of the questionnaire for ECEC teachers will be used. The questionnaire includes questions to obtain ECEC teachers' age, sex, highest level of education, country of birth and parents' country of birth. The highest level of education (proxy for socio-economic status) of ECEC teachers will be subdivided in intermediate or higher education groups (17). Ethnicity will be based on first- and second-generation migration backgrounds. First-generation migration backgrounds will be defined as the country of birth. Second-generation migration backgrounds will be defined as the mother's country of birth, or, in case the mother's country of birth is the Netherlands, as the father's country of birth (18). The aim of this study is to examine the effects of a preschool-based intervention on the ECEC teacher-parent partnership regarding eating, physical (in)activity and sleeping behaviours in children. Ethnicity could play a role in this partnership. For example, when an ECEC teacher and parent have the same ethnicity, it could improve their partnership. A diverse group of ECEC teachers (and parents, see next paragraph) is expected, because teachers often live in the city district (Amsterdam Nieuw-West or Zuidoost) of their preschool. The city districts Amsterdam Nieuw-West and Zuidoost are known for their ethnic diversity. Ethnicity may occur as a moderator and/or mediator, and is therefore an indispensable variable (19).

Furthermore, the questionnaire for ECEC teachers includes questions on the ECEC teacher-parent partnership regarding eating, physical (in)activity and sleeping behaviours in young children. These questions are based on the Dutch 'Monitor Samenwerken met ouders 2018-2019' (20) and the 'Family-Centered Practices Scale (Extended Version)' by Dunst and Trivette (21). Answering options for the questions are totally disagree (1 point), slightly disagree (2 points), neutral (3 points), slightly agree (4 points), totally agree (5 points) or never (1 point), rarely (2 points), sometimes (3 points), mostly (4 point), always (5 points). For the questions based on the Dutch 'Monitor Samenwerken met ouders 2018-2019', a mean score per question will be calculated. For the questions based on the 'Family-Centered Practices Scale (Extended Version)', a mean score per scale will be calculated. The 'Family-Centered Practices Scale (Extended Version)' includes 2 scales: 1 for relational family support practices and 1 for participatory family support practices. ECEC teachers can use these practices to build a partnership with parents (21).

The questionnaire for ECEC teachers also includes questions to obtain data on the teachers' knowledge, attitude and practices about healthy behaviours in young children. These questions are based on the Food and Health Survey 2018 (22) and the

Child-care Food and Activity Practices Questionnaire (23). In addition, some questions are compiled by the research staff. Per question or scale (applicable for questions on food/activity-related practices) a mean score will be calculated. ECEC teachers can fill in the questionnaire during 'task hours' at preschool (it will take about 30 minutes to fill in the questionnaire). The research staff will visit preschools to collect the questionnaires (1 week after the questionnaires are being provided). At the collection moment, the research staff will ask, in short interviews of about 15 minutes, some additional questions regarding the ECEC teacher-parent partnership. These questions will be based on the teachers' answers in the completed questionnaire. In times of corona, the short interviews with ECEC teachers will be held by telephone.

## PARENTS

At baseline and at 6 months, participating parents will be provided with a paper questionnaire (provided in the 4 most spoken languages: phonetic Arabic, Turkish, Dutch and English). The questionnaire includes questions to obtain parents'/children's age, sex, level of education (only applicable for parents, country of birth and parents' country of birth. The highest level of education (proxy for socio-economic status) of parents will be subdivided in lower, intermediate or higher education groups (17). Ethnicity will be based on first- and second-generation migration backgrounds. First-generation migration backgrounds will be defined as the country of birth. Second-generation migration backgrounds will be defined as the mother's country of birth, or, in case the mother's country of birth is the Netherlands, as the father's country of birth (18). The intervention should reach parents and their children with different socio-economic and socio-cultural backgrounds. To investigate if we indeed reach all parents and children it is important to gain insight in the level of education and ethnicity of parents and their children. Moreover, the intervention is intended to improve the ECEC teacher-parent partnership regarding eating, physical (in)activity and sleeping behaviours in children. Ethnicity could play a role in this partnership. For example, when an ECEC teacher and parent have the same ethnicity, it could improve their partnership. A diverse group of parents (and teachers, see previous paragraph) is expected, because parents often live in the city district (Amsterdam Nieuw-West or Zuidoost) of their preschool. The city districts Amsterdam Nieuw-West and Zuidoost are known for their ethnic diversity. Level of education and ethnicity may occur as moderators and/or mediators, and are therefore indispensable variables. It is, therefore, important to obtain information about the above mentioned socio-demographic characteristics. Ethnicity and level of education may occur as moderators and/or mediators, and are therefore needful variables (19).

Furthermore, the questionnaire for parents includes questions on the ECEC teacher-parent partnership regarding eating, physical (in)activity and sleeping behaviours in young children. These questions are, just like in the questionnaire for ECEC teachers, based on the Dutch 'Monitor Samenwerken met ouders 2018-2019' (20) and the 'Family-Centered Practices Scale (Extended Version)' by Dunst and Trivette (21).

Answering options for the questions are the same as in the questionnaire for ECEC teachers and mean scores per question/scale will be calculated.

The questionnaire for parents also includes questions to obtain data on the eating, physical (in)activity and sleeping behaviours of their child. These questions are based on the 'Sarphati Amsterdam Core set plus questionnaire for 36 months' (24). In addition, some questions are included on the parents' knowledge, attitude and practices about healthy behaviours for young children. These questions are based on the Food and Health Survey 2018 (22), Comprehensive Feeding Questionnaire (25), Preschooler Physical Activity Parenting Practices questionnaire (26), and a questionnaire on maternal efficacy (27). In addition, some questions are compiled by the research staff. Parents can fill in the questionnaire at home (it will take about 30 minutes to fill in the questionnaire). The research staff will visit preschools to collect the questionnaires (1 week after the questionnaires are being provided). To obtain more information about children's dietary intake, parents will be asked to participate in a 24-hour dietary recall at baseline and at 6 months. In times of corona, 24-hour dietary recall sessions will not be performed as parents and researchers are not allowed to enter the preschools. When it is allowed again to enter preschools, the researchers will start to collect data on children's dietary intake. Paper questionnaires will, in times of corona, be distributed (at the door) by ECEC teachers. To obtain input for a process evaluation of the intervention, short interviews with participating parents will be held at 6 months (only applicable for parents in the intervention group). At 6 months, the research staff will ask parents if they would like to participate in a short interview of about 15 minutes and give their opinion about the parent-child activities. If yes, the research staff will note a telephone number and will call the specific parent for the short interview concerning the intervention.

